### Sample size

Investigators conducting the trial estimate the sample size based on the level of NT-proBNP, the main efficacy indicator. The literature (Li et al., 2013), showed that NT-proBNP levels decreased by more than 30% after 12 weeks of conventional basic treatment combined with placebo in 31.98% of patients, and NT-proBNP levels decreased by more than 30% after 12 weeks of conventional basic treatment combined with herbal medicine in 47.95% of patients. Therefore, it is expected that the percentage of patients with NT-proBNP levels decreasing more than 30% after 12 weeks of conventional basic treatment combined with XBP will be 50%. Thus, assuming *α* = 0.05 and *β* = 0.20, the calculated sample size required for each group was 114 cases after substituting the above values using PASS11 software. Considering that 20% will miss visits, the sample size was adjusted to 142 cases in each group. The total number of cases required for both groups was 284.

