### Randomization and allocation

Participants will be randomly assigned, in a 1:1 ratio, to the experimental and control groups using the central randomization system of the Drug Clinical Trial Management Office, Shunde Hospital of Guangzhou University of Chinese Medicine. Randomization groups will be stratified by the central stratification method, generating random numbers, and generating randomized results by SAS statistical software (version 9.4; SAS Institute, Cary, NC, United States). The randomization number and drug number will be separately obtained by each study subcenter investigator using a sequential number in the central randomization system. All center numbers, sequence numbers, randomization numbers, and drug numbers will be managed by the statistical unit.

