### Secondary outcome indicators

1) cardiac function classification (NYHA) (Yancy et al., 2013); 2) the 6-minute walking distance test (6MWT) (Ingle et al., 2005); 3) the Minnesota Living with Heart Failure Questionnaire score (Fitz et al., 2021); 4) the rate of endpoint events (acute exacerbation rehospitalization of CHF, cardiac death and all-cause death, *etc.*); 5) serum NT-proBNP level; 6) cardiac function indicators, such as the left ventricular ejection fraction (LVEF), the left ventricular end-diastolic diameter (LVEDD), and the left ventricular end-systolic diameter (LVESD); and 7) TCM symptom scores (Supplementary material 1) will be used to quantify the symptoms. Differences in TCM symptom scores between groups at baseline and week 4, week 8, week 12 and week 24 post-treatment will be compared and differences between groups will be calculated. The scoring process will be carried out independently by two chief TCM physicians with more than 5 years of medical experience, with any discrepancies being resolved through consultation. The comprehensive efficacy criteria were as follows: 1) ineffective: no significant improvement or even worsening of symptoms and signs, and a reduction in symptom score <30%; 2) effective: improvement of symptoms and signs, and a reduction in symptom score ≥30%; 3) significant effect: significant improvement of symptoms and signs, and a reduction of syndrome score ≥70%. TCM symptom scores = [(posttherapy score - pretherapy score)/pretherapy score]  ×  100%. Outcome indicators will be collected at week 4, 8, 12 and 24 after inclusion in the study.

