### Statistical analysis methods

All statistical tests will be performed using a two-sided test, and a *p* value less than or equal to 0.05 will be considered statistically significant for the difference tested. Dichotomous indicators will be used to describe the number of cases and percentages of each category. Quantitative indicators conforming to normal distribution will be expressed as the “mean ± standard deviation” and skewed data will be described as the median, lower quartile (Q1), and upper quartile (Q3). Comparisons between the two general groups will be analyzed using appropriate methods depending on the type of indicator. Paired *t* test or Wilcoxon rank sum test will be used for comparison between groups for quantitative data, chi-square test or Fisher exact probability method for categorical data, and Wilcoxon rank sum test or CMH test for rank data. The specific applicable statistical methods for each outcome indicator are shown in Table 3.

**TABLE 3 T3:** Outcomes and methods of analyses.

Outcome/variable	Hypothesis	Measures	Methods of analyses
Baseline balance test		Quantitative outcomes (age, temperature, heart rate, respiratory rate, and blood pressure)	*t*-test/Wilcoxon rank-sum test
		Qualitative outcomes (sex, marriage, and previous treatment)	Chi-squared test/Fisher’s exact test/rank-sum test
Primary outcome			
Percent and cases of NT-proBNP decreased ≥30%	decrease occurred		Chi-square test/Fisher’s exact test
Secondary outcome			
NYHA class	decrease occurred		Wilcoxon rank-sum test
6MWT	increase occurred		*t*-test/Wilcoxon rank-sum test
MLHFQ score	decrease occurred	Questionnaire	*t*-test/Wilcoxon rank-sum test
Clinical-endpoint events	decrease occurred	Clinical-endpoint event rate	Log-rank test
NT-proBNP	decrease occurred		*t*-test/Wilcoxon rank-sum test
Echocardiographic parameters	Improvement occurred	LVEF, LVEDD, LVESD	*t*-test/Wilcoxon rank-sum test
TCM symptom scores	decrease occurred	Disappearing rate of main symptoms	Chi-square test/Fisher’s exact test
Safety outcomes			
AEs, SAE		Percent and cases of AEs and SAEs	Chi-square test/Fisher’s exact test

NYHA, New York heart association; 6MWT, 6-min walk distance; MLHFQ, Minnesota living with heart failure questionnaire; LVEF, left ventricular ejection fraction; LVEDD, left ventricular end-diastolic diameter; LVESD, left ventricular end-systolic diameter; AE, adverse event; SAE, serious adverse events; TCM, traditional Chinese medicine.

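### Table 3 compares NYHA class with an unadjusted rank-sum test, although baseline class is collected and varies at entry; the test is valid but forgoes precision

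*Protocol article*

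**What the plan says.** All references are to the protocol article.

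- **Outcome.** Secondary outcome indicators lists "cardiac function classification (NYHA") first. Table 2 schedules it at Visit 1 and at weeks 4, 8, 12 and 24.
- **Entry range.** The inclusion criteria admit classes II and III and also some class IV patients, so class varies at baseline.
- **Test.** For ordinal data the general text of Statistical analysis methods offers "Wilcoxon rank sum test or CMH test for rank data". It names no strata and refers to Table 3 for the specific method. The NYHA row of Table 3 gives the Wilcoxon rank-sum test alone and states the hypothesis as a decrease. It does not say whether follow-up class or change from baseline is ranked.
- **Randomisation.** "Randomization groups will be stratified by the central stratification method". This reads as stratification by centre, of which there are six. Baseline NYHA class is not named as a factor.
- **Power.** The Sample size section covers only the NT-proBNP responder outcome. It gives no effect size, class distribution, correlation or power for NYHA class.

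**The concern.** A rank-sum test on follow-up class treats differences already present at entry as part of the random variation between patients. If later class is correlated with entry class, some of that variation can be explained by a variable the trial already records. Leaving it out lowers the chance of detecting a real difference.

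Ranking change does use the baseline value, but it forces a one-for-one subtraction. That adds noise when the correlation is low. Conditioning on baseline class avoids both problems, and the analysis then no longer depends on which of the two readings was meant.

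The general text already names a test family that can carry strata, but the NYHA row does not use it. What is at stake is power and precision on the first-listed secondary outcome.

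**Working it through.** **1. The plan's own figure.** Inputs from the Sample size section: "conventional basic treatment combined with placebo in 31.98% of patients"; the rate expected "after 12 weeks of conventional basic treatment combined with XBP will be 50"%; "assuming *α* = 0.05 and *β* = 0.20". Sidedness is from Statistical analysis methods: "All statistical tests will be performed using a two-sided test". With unpooled variance:

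n = (1.96 + 0.8416)² × (0.3198 × 0.6802 + 0.50 × 0.50) / (0.50 − 0.3198)² = 7.849 × 0.4675 / 0.03247 = 113.0, rounded up to 114.

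This agrees with the plan: "the calculated sample size required for each group was 114 cases". Allowing for 20% loss, 114 / 0.8 = 142.5, against 142 stated. The figure belongs to the primary outcome. Only the 114 per arm is carried forward.

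**2. Model for NYHA class.** The document gives no NYHA inputs, so everything below except the 114 per arm, the 1:1 ratio, the six centres and the two-sided 5% level is an assumption. Baseline and follow-up class are cut from two normal variables with correlation ρ. Treatment shifts the follow-up variable by d SD.

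**3. Set A.** Baseline I/II/III/IV 0/50/40/10%; week-12 placebo 10/50/33/7%; d = 0.35; 3,000 simulated trials per setting, so the simulation error of a power near 66% is √(0.66 × 0.34 / 3000) = 0.9 points.

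| ρ | Rank-sum, follow-up class | van Elteren by baseline class | Gain |
|---|---|---|---|
| 0.4 | 66.1% | 70.5% | +4.4 |
| 0.6 | 64.7% | 74.7% | +10.0 |
| 0.75 | 66.0% | 84.8% | +18.8 |

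A separate repeat gave 66% v 70%, 67% v 78% and 67% v 85%.

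**4. Set B.** Baseline II/III/IV 45/45/10%; control follow-up I/II/III/IV 15/50/28/7%; d = 0.37; small centre effect; 1,500 trials per setting. The two gain columns are for the van Elteren test.

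| ρ | Rank-sum, follow-up | Rank-sum, change | van Elteren by class | Gain v follow-up | Gain v change |
|---|---|---|---|---|---|
| 0.2 | 74.3% | 58.5% | 75.8% | +1.5 | +17.3 |
| 0.4 | 72.8% | 65.6% | 77.7% | +4.9 | +12.1 |
| 0.5 | 71.7% | 72.2% | 78.9% | +7.2 | +6.7 |
| 0.6 | 72.5% | 78.5% | 83.9% | +11.4 | +5.4 |
| 0.7 | 74.9% | 85.9% | 90.1% | +15.2 | +4.2 |
| 0.8 | 71.5% | 90.7% | 91.5% | +20.0 | +0.8 |

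With d = 0.30 and ρ = 0.2 the gain over follow-up class falls to 56.6 − 56.3 = +0.3.

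**5. Sensitivity.**
- *Fewer classes in play.* With 75% in class II at baseline and d = 0.40, the gains over follow-up class are 81.2 − 80.2 = +1.0 (ρ = 0.3), 84.0 − 80.0 = +4.0 (0.5) and 88.8 − 78.0 = +10.8 (0.7).
- *Centre.* Stratifying by centre alone changes power by about 0 to 2 points, for example 72.8% to 73.7% at ρ = 0.4 in Set B. Nearly all the gain comes from baseline class.
- *Type I error.* About 4 to 5% for every test in Sets A and B, including the unadjusted one.

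**6. Sparse strata.** If recruitment were even (an assumption), 228 evaluable patients over six centres is 38 per centre. With 10% in class IV, that is about four class IV patients per centre, so fully crossed strata would be thin.

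**The case against.** The strongest reply is that nothing here is wrong. The rank-sum test is a legitimate test of an ordinal outcome, and its type I error is held. The trial sets no power target for NYHA class. The general text already allows a CMH test, and covariates for a secondary outcome often go into the analysis plan. The size of the gain rests entirely on assumed inputs. No row of Table 3 names a covariate or stratum, so singling out NYHA class may look arbitrary.

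Much of this stands, and it limits the point. It does not remove it: the text refers to Table 3 for the specific methods, and the NYHA row names one unadjusted test. The comment is therefore about a stated method, not about missing detail.

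Three stronger readings are tempting, and the document supports none of them.

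- *A reader might infer that the test is invalid or biased.* It is not. Chance imbalance in baseline class is already covered by its type I error.
- *A reader might infer a definite gain, such as 4 to 19 points, from using baseline class and the randomisation strata together.* That range holds only for chosen correlations and a test of follow-up class. Centre contributes little, and baseline class is not a named randomisation factor.
- *A reader might infer that adjustment is free.* It needs no extra patients or data, but it brings a modelling assumption or possibly sparse strata.

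**Conclusion.** The point holds as a matter of efficiency. Table 3 commits NYHA class to an unadjusted rank-sum test, although a baseline value that varies between patients is recorded at Visit 1, and it leaves open whether follow-up class or change is ranked.

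Adjustment gained power in both sets of assumptions and under both readings of the planned test. The gain runs from almost nothing to about 20 points. The baseline-to-follow-up correlation drives it upward if follow-up class is ranked and downward if change is ranked. The document gives neither that correlation, nor the class distribution, nor the expected effect, so no single figure can be assigned to this trial. The matter concerns one secondary outcome and does not affect the primary analysis or the sample size.

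**What to change.** In the NYHA row of Table 3, replace the rank-sum test by one of the following, specified before unblinding:

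1. a proportional-odds model of week-12 class with treatment, baseline class and centre as main effects, reporting the common odds ratio with its 95% confidence interval; or
2. a van Elteren or CMH row-mean-score test of week-12 class stratified by baseline class. The general text already lists the CMH test.

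Either one also settles what is analysed: week-12 class given baseline class.

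The cost is one line in the table or the analysis plan. The first option carries a proportional-odds assumption. The second can run into sparse strata if class is fully crossed with centre, so stratify by class alone or enter centre as a main effect in the model.

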### Inclusion criteria

Patients will be included in this study if they meet the following criteria: 1) meet the diagnostic criteria for CHF, and the Chinese medical evidence of “heart-kidney yang deficiency syndrome”; 2) 18 years old ≤ age ≤80 years old, regardless of sex; 3) have a history of CHF for more than 3 months or clinical findings of heart failure symptoms for more than 3 months; 4) NYHA heart function classification II-III, or stable clinical symptoms, including those who have been diagnosed within 2 weeks before enrollment or NYHA Class IV; 5) serum N-terminal prohormone of brain natriuretic peptide (NT-proBNP) level ≥450 pg/ml; 6) have received conventional basic treatment for at least 2 weeks and have not undergone a dose adjustment; and 7) voluntary participation, clearly understanding and signed the informed consent form.

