## Outcomes

### Primary outcomes

Details of the observational items and the time window for data collection are shown in Table 2. The primary outcome will be the proportion change of patients with a decrease of more than 30% in serum NT-proBNP after treatment.

**TABLE 2 T2:** Study procedure table.

Study phase time	Baseline period	Intervention period			Follow-up
	Visit 1	Visit 2	Visit 3	Visit 4	Visit 5
	−7 to 0 days	4 weeks	8 weeks	12 weeks	24 weeks
Data collection at baseline					
Inclusion/exclusion criteria	×				
Informed consent	×				
Demographic data	×				
Obtain the central random number	×				
Previous history, medical history, and allergies	×				
Efficiency evaluation					
NT-proBNP	×	×	×	×	×
Echocardiographic parameters	×	×	×	×	×
NYHA class	×	×	×	×	×
6MWT	×	×	×	×	×
MLHFQ score	×	×	×	×	×
TCM symptom scores	×	×	×	×	×
Clinical-endpoint events	×	×	×	×	×
Safety evaluation					
Vital signs	×	×	×	×	×
Physical examination	×	×	×	×	×
Blood routine	×	×	×	×	×
Urine routine	×	×	×	×	×
ECG	×	×	×	×	×
Blood biochemistry	×	×	×	×	×
Chest radiograph	×			×	×
Other work					
Dispense drug	×	×	×	×	
Recovery and record of study drug		×	×	×	
Record AEs		×	×	×	
Complications due to medications		×	×	×	
Evaluate compliance		×	×	×	×

NYHA, New York heart association; 6MWT, 6-min walk distance test; MLHFQ, Minnesota living with heart failure questionnaire; ECG, electrocardiogram; AE, adverse event; “x” represents the need for implementation at this point in time.

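### Table 3 fixes unadjusted two-group tests for six quantitative secondary outcomes that are all measured at baseline; baseline adjustment would be more precise at almost no cost

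*Protocol article*

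**What the plan says.** Under Statistical analysis methods, the protocol article makes Table 3 the authority on methods: "The specific applicable statistical methods for each outcome indicator are shown in Table 3". For 6-minute walk distance, MLHFQ score, NT-proBNP level and the echocardiographic measures (LVEF, LVEDD, LVESD), the entry there is "t*-test/Wilcoxon rank-sum test". The section names no baseline or centre covariate, no repeated-measures model and no transformation. Skewed data are to be described by median and quartiles.

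The running text above the table differs slightly: "Paired *t* test or Wilcoxon rank sum test will be used for comparison between groups for quantitative data". A paired t-test does not fit a comparison of two independent arms, and it is not a baseline-adjusted comparison either.

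The data that an adjusted analysis needs are already planned. Table 2 schedules all of these measures at Visit 1 (days -7 to 0), and the section on secondary outcomes adds: "Outcome indicators will be collected at week 4, 8, 12 and 24 after inclusion in the study". For NT-proBNP, the Inclusion criteria set a floor, "level ≥450 pg/ml", and no ceiling. The primary outcome is a relative fall of more than 30% in the same marker.

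**The concern.** Patients with heart failure differ widely at entry in natriuretic peptide, walking distance and ventricular size, and a patient's later value usually tracks the first one. A test that does not model this counts predictable between-patient variation as noise.

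Two things are at stake for these secondary outcomes:

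- **Precision.** Confidence intervals are wider, and power lower, than the collected data allow.
- **Chance imbalance.** If the arms differ at baseline by an amount D through chance, a follow-up-only comparison carries part of D into the estimated effect. A change-score comparison over-corrects and carries part of D with the opposite sign, through regression to the mean.

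Table 3 also does not say which of these two comparisons is meant, or which of the four later visits is the main one. The same entry could therefore produce several different results.

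**Working it through.** **Inputs from the document.** Section Sample size: 31.98% versus 50% responders, α = 0.05, β = 0.20, 114 evaluable per group, inflated to 142 for 20% missed visits. Section Statistical analysis methods: two-sided tests.

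**Input assumed.** r, the correlation between baseline and follow-up, is not given. The range shown is 0.3 to 0.8.

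**The plan's own figure.** With unpooled variance, n = (1.960 + 0.842)² × (0.3198 × 0.6802 + 0.50 × 0.50) / (0.50 − 0.3198)² = 113.01, which rounds up to the stated 114. Then 114 / 0.8 = 142.5, against the stated 142. This calculation concerns the primary outcome only. The plan states no figure for any quantitative secondary outcome, so 114 per group is used below simply as the evaluable number.

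**Variance of the treatment difference.** Assume equal SD at baseline and follow-up. Relative to a follow-up-only comparison (set to 1):

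- change score: 2(1 − r)
- ANCOVA: 1 − r²
- ANCOVA relative to change score: (1 − r²) / [2(1 − r)] = (1 + r)/2

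**Detectable difference at 80% power.** This is (1.960 + 0.842) × √(2/114) = 0.371 SD for follow-up only, multiplied by √[2(1 − r)] for change and by √(1 − r²) for ANCOVA.

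| r | ANCOVA variance vs follow-up | ANCOVA variance vs change | Detectable, follow-up (SD) | Detectable, change (SD) | Detectable, ANCOVA (SD) |
|---|---|---|---|---|---|
| 0.3 | 0.91 | 0.65 | 0.371 | 0.439 | 0.354 |
| 0.5 | 0.75 | 0.75 | 0.371 | 0.371 | 0.321 |
| 0.7 | 0.51 | 0.85 | 0.371 | 0.287 | 0.265 |
| 0.8 | 0.36 | 0.90 | 0.371 | 0.235 | 0.223 |

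At r = 0.5 to 0.7 the variance reduction is therefore 1 − 0.75 = 25% to 1 − 0.51 = 49% against follow-up values. Against changes it is 1 − 0.75 = 25% to 1 − 0.85 = 15%, and at r = 0.8 it is 1 − 0.90 = 10%.

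In patient terms, at r = 0.5 ANCOVA with 114 × 0.75 ≈ 86 per group matches either unadjusted test with 114. For an illustrative effect of 0.3 SD with 114 per group, power at r = 0.5 is 62% for either unadjusted test and 74% for ANCOVA. At r = 0.7 it is 62% (follow-up), 83% (change) and 89% (ANCOVA).

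**Chance imbalance.** Given a baseline difference D, the expected error in the estimate is rD for follow-up only, −(1 − r)D for change score and 0 for ANCOVA. At r = 0.5 to 0.7 this is 0.5D to 0.7D for follow-up values and −0.5D to −0.3D for changes.

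The formulas are exact for t-type comparisons and only a guide for rank-sum tests. They leave out any further gain from adjusting for centre.

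**The case against.** The strongest defence is that two-group t and rank-sum tests are valid in a randomized trial. They are unbiased on average and keep the type I error, and only secondary outcomes are involved. That stands. This is a question of efficiency, not of error.

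A second defence is that Table 3 may intend changes from baseline. Its hypothesis column speaks of decreases and increases having occurred, and the text mentions a paired test. If so, baseline is already used, the 49% figure does not apply, and the gain is 25 to 15% at r = 0.5 to 0.7. This also stands, but ANCOVA remains the more precise method over the whole range of r examined.

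A third is that details may lie in an analysis plan that is not shown. This fails for the choice of test, because the article says that Table 3 gives the specific method for each outcome. It succeeds for missing-data handling and for which estimates and intervals are reported.

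A reader might infer more than the document supports:

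- **That patients with missed visits will be discarded.** The 20% is only a sample-size allowance, and no rule for missing visits is stated.
- **That the loss can be shown from the plan's responder rates.** On a normal model for log change, 31.98% versus 50% corresponds to 0.468 SD, and 114 per group gives about 94% power against about 79% for the responder test. But the 94% belongs to an unadjusted test of log change. The contrast therefore measures the cost of dichotomising the primary marker, not the lack of baseline adjustment.
- **That every quantitative secondary outcome is treated this way.** The TCM symptom score is numeric, and the text says "Differences in TCM symptom scores between groups at baseline and week 4, week 8, week 12 and week 24 post-treatment will be compared", but Table 3 analyses a disappearance rate of main symptoms by chi-square or Fisher's test. That is a separate matter.

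**Conclusion.** The point holds as a low-cost gain in precision for six secondary measures: NT-proBNP level, 6-minute walk distance, MLHFQ score, LVEF, LVEDD and LVESD. The document does not support a claim of systematic bias, of inflated type I error or of harm to the primary analysis.

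The direction of the gain does not depend on which comparison Table 3 means; its size does. With r assumed at 0.5 to 0.7, the variance reduction is 25 to 49% if follow-up values are compared and 25 to 15% if changes are compared. At r = 0.8 with changes it is about 10%. Because r and the SDs are not given, these are ranges under assumption, not estimates for this trial.

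The case for a log scale for NT-proBNP rests on inference. Entry has a floor and no ceiling, and the primary outcome is a relative fall, so a ratio is the natural measure. The document gives no distribution for the marker.

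**What to change.** In Table 3, replace the entries for these six measures with ANCOVA at week 12, with treatment, the outcome's own baseline value and centre as terms. Alternatively, use a mixed model for repeated measures over the scheduled visits, adding visit and treatment-by-visit terms, with the week 12 treatment difference as the stated contrast. Analyse NT-proBNP as log values and report the geometric mean ratio with its 95% CI. Keep the rank-sum tests as sensitivity analyses, stating whether they compare follow-up values or changes. Correct the reference to a paired t-test for between-group comparison in the same edit. The primary endpoint stays as it is.

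The cost is a wording change and slightly more programming, with no new data or visits. The mixed model, if chosen, adds a missing-at-random assumption and a choice of covariance structure; single-visit ANCOVA avoids the covariance choice. The article reports the trial as blinded and still recruiting, so the change can be prespecified before unblinding.
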